## Abstract

**Background:**

Cognitive deficits are a distinct feature among people at ultra-high risk (UHR) for psychosis and pose a barrier to functional recovery. Insufficient evidence exists on how to ameliorate these cognitive deficits in patients at UHR for psychosis and hence improve daily living and quality of life. The aim of the trial is to investigate whether cognitive remediation can improve cognitive and psychosocial function in patients at UHR for psychosis.

**Methods:**

The FOCUS trial (Function and Overall Cognition in Ultra-high risk States) is a randomised, parallel group, observer-blinded clinical trial enrolling 126 patients meeting the standardised criteria of being at UHR for psychosis. Patients are recruited from psychiatric in- and outpatient facilities in the Copenhagen catchment area. Patients are randomised to one of the two treatment arms: cognitive remediation plus standard treatment versus standard treatment. The cognitive remediation consists of 24 weekly group-based and manualised sessions targeting neurocognition and social cognition. In addition to the group sessions, the patients will be offered 12 individual sessions aiming at maximising the transfer of the effects of the cognitive training to their everyday lives. Follow-up assessments will be conducted at 6 and 12 months after randomisation. The primary outcome is the composite score on the Brief Assessment of Cognition in Schizophrenia at cessation of treatment after 6 months. Secondary outcomes are social and daily functioning, psychosis-like symptoms, negative symptomatology, and depressive symptomatology as measured with the Personal and Social Performance Scale, Brief Psychiatric Rating Scale-Expanded Version, Scale for the Assessment of Negative Symptoms, and the Montgomery-Åsberg Depression Rating Scale.

**Discussion:**

This is the first trial to evaluate the effects of neurocognitive and social cognitive remediation in UHR patients. The FOCUS trial results will provide evidence on the effect of targeted and comprehensive cognitive rehabilitation on cognition, daily living, and symptomatology as well as long-term outcome in preventing transition to psychosis in UHR patients.

**Trial registration:**

ClinicalTrials.gov NCT 02098408. Date of registration 18 March 2014.

## Background

### The prodromal phase of schizophrenia and other psychotic disorders

Schizophrenia is a debilitating disorder with a point prevalence of 0.6% [1]. The construct of the ultra-high-risk (UHR) state for schizophrenia and other psychotic disorders captures the putative prodromal phase of psychosis, which is seen as a forerunner of frank psychosis. Patients in this UHR state present discrete yet identifiable psychotic symptoms. Intervention studies targeting the UHR state for psychosis have increased during the last decade [2]. Potentially, such interventions could avoid, ameliorate, or delay progression to psychosis. Furthermore, initiating appropriate treatment as early as possible has the potential to improve both the clinical and functional outcomes of patients.

The most recent meta-analysis on prodromal intervention in psychosis assessed 10 randomised clinical trials aiming at preventing psychosis [3]. The intervention strategies in these trials encompass antipsychotic medication, omega-3 fatty acids, psychosocial, and cognitive behavioural interventions and integrative therapy [4-13]. The results from these trials are promising, but evidence is still too scarce to be conclusive. None of the studies on prodromal intervention have explored the potential effects of extensive cognitive remediation on improving cognitive and psychosocial functioning in prodromal patients or the potential to prevent transition to psychosis.

### Cognitive dysfunctions and cognitive remediation in schizophrenia

It is well known that impairments in cognition are characteristic and pervasive in schizophrenia and significantly influence the functional outcome [14-16]. The cognitive and the associated functional impairments cause patients with schizophrenia to experience disturbances in areas such as independent living, social relationships, and educational attainment [15,17] and are a strong predictor of response to psychiatric rehabilitation [18].

Cognition encompasses neurocognitive and social cognitive processes, which are regarded as two distinct but interrelated domains [19]. Neurocognition can be defined as “processes of linking and appraising information. It includes abilities like speed of processing, attention, verbal and visual learning and memory, working memory as well as reasoning and problem solving” [20], whereas social cognition can be defined as “the mental operations that underlie social interactions, including perceiving, interpreting, and generating responses to the intentions, dispositions, and behaviours of others” [21]. It is hypothesised that social cognition acts as a mediator between neurocognition and functional outcome. Evidence for this hypothesis has been found in several studies [20,22-27]. These findings imply that social cognition is proximal to the patients’ everyday functioning. In this context social cognition can be seen as critical for the daily functioning of the patients (e.g., community functioning, interpersonal relationships, and ultimately quality of life) [28]. Building on this rationale we decided to target both neurocognition and social cognition in our trial.

A promising method to alleviate cognitive deficits is using cognitive remediation (CR). It can be defined as “a behavioural training based intervention that aims to improve cognitive processes (attention, memory, executive function, social cognition or metacognition) with the goal of durability and generalization” [29]. In the most recent meta-analysis of CR in schizophrenia, Wykes et al. reviewed 40 trials. The effect of CR on cognition, functioning, and symptoms was assessed post-treatment and at follow-up. They demonstrated a significant positive effect in most cognitive domains [global cognition effect size 0.45 with 95% confidence interval (CI) = 0.31-0.59] and on functional outcomes (effect size 0.42 with 95% CI = 0.22-0.62). The effect appears to be durable (effect size 0.43 with 95% CI = 0.18-0.67). It is noted that the impact of CR on functional outcomes was significantly greater in studies also providing psychiatric rehabilitation [29]. This leads to the conclusion that CR seems an important and beneficial target of intervention in people with schizophrenia. Research indicates that CR is also effective in other severe mental illnesses [30,31].

### Cognitive dysfunctions and cognitive remediation among people at ultra-high risk for psychosis

A clinical staging model of the cognitive deficits in schizophrenia has been proposed. It suggests that there is a cognitive decline between early stages of the illness, implying that the cognitive deficits become increasingly severe as the illness develops [32]. Most studies favour a neurodevelopmental model suggesting that the cognitive deficits are already established before illness onset and remain mostly stable during the illness [33,34].

There is an increasing body of evidence demonstrating that patients in the UHR state show significant deficits in multiple cognitive domains [35-38]. In their meta-analysis on cognitive dysfunctions in the UHR state, Fusar-Poli et al. found cognitive deficits associated with the UHR state in attention, verbal fluency, visual and verbal memory, working memory, and executive functioning [35]. An area of cognition that also has been found to be impaired in the UHR state is social cognition, which appears to be closely related to functional outcome [22,39]. Evidence shows that the cognitive deficits in UHR patients have a significant impact on their level of functioning [37,40], an even greater impact than symptom severity [22,37].

Reviewing the literature in the electronic databases (PubMed, EMBASE, Clinical Trials.gov, and WHO Trial Portal) for studies related to the terms “cognitive remediation, prodromal psychosis, or ultra-high risk states” resulted in only two published studies that have examined the effect of CR on UHR patients. Bechdolf et al. offered CR as part of a broader integrated intervention programme [9]. They found a beneficial effect of the integrated intervention, but it was not possible to isolate the effect of the CR. A pilot study by Rauchensteiner et al. compared the effectiveness of CR in 10 UHR patients to that of CR in 16 patients with schizophrenia and found relatively greater improvements in cognitive functioning (improved long-term memory functions as well as attention) in the former group [41]. However, as the authors also state, this finding needs to be replicated in studies using larger sample sizes. Furthermore, the observational design generally hinders fair assessment of the benefits of interventions [42]. Of note, the two studies included short-term remediation programmes (10-12 sessions) without direct assessment of the effect on daily functioning. Accordingly, there is a need for randomised clinical trials that apply more extensive cognitive training on larger UHR samples.

The aim of the FOCUS trial is to investigate to what extent CR may improve cognitive abilities and the associated psychosocial function in patients at UHR for psychosis. Bearing in mind the disabling consequences of cognitive deficits in schizophrenia and psychosis-like states, it seems vital to target these deficits to improve the everyday functioning of the patients. Knowing that the cognitive deficits manifest themselves in the UHR state, we expect that cognitive deficits may be even more amenable to treatment at this early stage of illness than what has previously been found at a more chronic stage [43,44]. Accordingly, targeting cognitive dysfunctions in the prodromal phase of psychosis may be the optimal time to intervene.

If a beneficial effect of CR on the cognitive and psychosocial dysfunctions in UHR patients is found, this would point to future randomised clinical trials and later potential implementation of CR in facilities offering early intervention in psychosis in order to enhance the ability of patients to function in their daily life.

### Hypotheses

In the present study we will examine whether:Cognitive remediation therapy will be superior to standard treatment in improving cognitive functioning in UHR patients (null hypothesis: no difference between the two intervention groups).Cognitive remediation therapy will be superior to standard treatment in improving psychosocial functioning and clinical symptoms in UHR patients (null hypothesis: no difference between the two intervention groups).

## Methods

### Recruitment

The FOCUS trial is a randomised, blinded, parallel-group superiority clinical trial, enrolling a total of 126 help-seeking patients from in- and outpatient facilities in the catchment area of Copenhagen (Figure 1). Patients meeting standardised ‘at-risk’ criteria based on the Comprehensive Assessment of At-Risk Mental States (CAARMS) [45] will be approached about participating in this clinical trial. Patients will be randomised (1:1) to intensive CR plus standard treatment versus standard treatment, as described in further detail in the section Interventions.

**Figure 1 Fig1:**
[figure not shown]
**Flowchart of the FOCUS trial.**

### Inclusion criteria

Participants aged 18-40 years who provide written informed consent and fulfil criteria for being at UHR for psychosis (defined by one or more of the following):**Vulnerability (Trait and State Risk Factor) Group:** Individuals with a combination of a trait risk factor (schizotypal personality disorder or a family history of psychotic disorder in a first degree relative) and a significant deterioration in functioning or sustained low functioning during the past year.**Attenuated Psychotic Symptoms (APS) Group:** Individuals with sub-threshold (intensity or frequency) positive psychotic symptoms. The symptoms must have been present during the past year.**Brief Limited Intermittent Psychotic Symptoms (BLIPS) Group:** Individuals with a recent history of frank psychotic symptoms that resolved spontaneously (without antipsychotic medication) within 1 week. The symptoms must have been present during the past year.

### Exclusion criteria

Exclusion criteria are: a past history of a treated or untreated psychotic episode of 1 week’s duration or longer, psychiatric symptoms that are explained by a physical illness with psychotropic effect or acute intoxication (e.g., cannabis use), a diagnosis of a serious developmental disorder (e.g., Asperger’s syndrome), currently receiving methylphenidate, or rejects providing informed consent.

An exit criterion is transition to psychosis. Participants who convert to psychosis will be assessed with the 12-month assessment battery.

### Interventions

#### Cognitive remediation (CR) in the experimental group

The CR is conducted in a group setting using both computerised exercises and group exercises. Patients assigned to the experimental intervention group will receive 2 h of CR (1 h of neurocognitive training and 1 h of social cognitive training) once a week for a total of 24 weeks. The training is done in an open group format. In addition to the group training there will be a total of 12 individual sessions of about 50 min aiming at maximising the bridging of the cognitive training to the everyday functioning of the patients, as well as working with individual goals.

The CR is delivered by a cognitive specialist in collaboration with a psychology student with knowledge of cognitive psychology. There will be a maximum of eight participants in each group; thus the therapist-to-patient ratio will be 1:4 or less.

If a patient meets the exit criterion “transition to psychosis”, he or she will be excluded from the intervention but still participate in assessments and statistical analyses, in accordance with the intention-to-treat principle.

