### Sample size calculation

The sample size calculation is based on our primary outcome, a priori defined to be the between-group difference at 6 months on the BACS composite score. We consider a clinically relevant difference on this scale to correspond to a Cohen’s *d* of 0.50 (e.g., assuming a between-group difference of 3.0 and a pooled SD of 6.0) [29]. With a two-sided alpha of 0.05 and power of 80%, this will require 63 participants to be randomised to each of the two interventions.

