### Statistical analyses

The planned comparisons between the two groups on continuous outcomes will be carried out with a generalised linear model adjusted for stratification variables, potential baseline imbalances, and skewed attrition, with missing data handled by multiple imputations. As an important secondary assessment of this type of outcome, linear mixed model analyses with repeated measurements and an unstructured covariance matrix will assess the interaction term between time and intervention. For non-normally distributed continuous outcome measures, non-parametric analyses will be applied. For dichotomous outcomes, logistic regression will be applied, and for time to transition, Cox proportional hazards regression will be applied. All analyses will be according to the intention-to-treat principle, analysing all participants in the groups they were assigned to by randomisation. We expect to encounter missing data, and this will be handled with the linear mixed models and multiple imputations as appropriate. A blinded and independent statistician who has no contact to the trial participants will conduct the primary efficacy analyses.

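### Cognitive remediation is given in shared groups in one arm only, but neither the 63-per-arm sample size nor the analysis as described allows for correlation among patients who share a group or therapist

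*Protocol article*

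**What the plan says.** All references are to the protocol article.

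- **Delivery of CR** (Cognitive remediation (CR) in the experimental group): "The CR is conducted in a group setting using both computerised exercises and group exercises". Sessions last two hours, weekly for 24 weeks. "The training is done in an open group format", and "There will be a maximum of eight participants in each group". A cognitive specialist and a psychology student lead each group. Each patient also has 12 individual sessions.
- **Content** (The neurocognitive training; The social cognitive training): the neurocognitive hour is individual computer work followed by group discussion, with at least an hour of computer training a week at home. The social cognitive hour is group psychotherapy and skills training.
- **Control arm** (Standard interventions in the control group): usual care from the patient's own clinicians, with no specific cognitive training and no group set up by the trial.
- **Sample size** (Sample size calculation): the primary outcome is the composite score of the Brief Assessment of Cognition in Schizophrenia (BACS) at 6 months. The basis is Cohen's d of 0.50, "assuming a between-group difference of 3.0 and a pooled SD of 6.0". "With a two-sided alpha of 0.05 and power of 80" per cent, "this will require 63 participants to be randomised to each of the two interventions". No ICC or design effect appears.
- **Analysis** (Statistical analyses): a generalised linear model adjusted for the stratification variables, baseline imbalance and attrition, and secondarily "linear mixed model analyses with repeated measurements and an unstructured covariance matrix". Neither description mentions CR group or therapist.

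**The concern.** Randomisation is of individuals ("Patients will be randomised (1:1) to intensive CR plus standard treatment versus standard treatment"), but after randomisation the CR patients share sessions, discussion and therapists for about six months. Their outcomes may therefore be correlated in a way the trial does not create among controls. This is a partially nested design.

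With positive correlation in the CR arm, the variance of the CR mean is larger than SD²/n. A model that treats all patients as independent then gives too narrow an interval and too many false positives, and the planned power is optimistic. The unstructured covariance in the mixed model does not help, because it describes repeated measurements on one patient and not correlation between patients.

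The power statements under Secondary outcomes and power calculations also use 63 per group without an allowance. They cover functioning and symptom scales.

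**Working it through.** **Inputs from the protocol:** difference 3.0, SD 6.0, two-sided alpha 0.05, power 80%, 63 per arm, 1:1 allocation, group size at most 8.

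**Assumed inputs:** ICC of 0.01, 0.05 or 0.10, and group sizes m of 4, 6 or 8. The protocol gives no ICC and only the maximum group size. The total SD is held at 6.

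**Step 1: reproduce the stated figure with independent patients.**
- n per arm = 2 × (1.96 + 0.8416)² × 6² / 3² = 62.8, rounded up to 63.
- SE = 6 × √(2/63) = 1.069.
- Power = Φ(3/1.069 − 1.96) = 80.1%. The t-test version gives 64 per arm, and 79.5% at 63.

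The 63 therefore contains no clustering allowance and almost no margin.

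**Step 2: inflate the variance in the CR arm only.**
- Design effect DE = 1 + (m − 1) × ICC.
- SE = 6 × √(DE/63 + 1/63).
- Power of a valid test = Φ(3/SE − 1.96).
- True two-sided type I error of the unadjusted test = 2 × [1 − Φ(1.96 × 1.069/SE)].
- n per arm for 80% power = (1 + DE) × (6 × 2.8016/3)², rounded up.

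Example with m = 8 and ICC = 0.05: DE = 1.35. SE = 6 × √(2.35/63) = 1.159, which is 8.4% above 1.069. Power = Φ(2.589 − 1.96) = 73.5%. Type I error = 2 × [1 − Φ(1.808)] = 7.1%.

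| m | ICC | DE | SE | Power | Type I error | n per arm for 80% |
|---|---|---|---|---|---|---|
| 8 | 0.01 | 1.07 | 1.088 | 78.8% | 5.4% | 65 |
| 8 | 0.05 | 1.35 | 1.159 | 73.5% | 7.1% | 74 |
| 8 | 0.10 | 1.70 | 1.242 | 67.6% | 9.2% | 85 |
| 6 | 0.01 | 1.05 | 1.082 | 79.2% | 5.3% | 65 |
| 6 | 0.05 | 1.25 | 1.134 | 75.4% | 6.5% | 71 |
| 6 | 0.10 | 1.50 | 1.195 | 70.9% | 8.0% | 79 |
| 4 | 0.01 | 1.03 | 1.077 | 79.5% | 5.2% | 64 |
| 4 | 0.05 | 1.15 | 1.108 | 77.2% | 5.9% | 68 |
| 4 | 0.10 | 1.30 | 1.146 | 74.4% | 6.8% | 73 |

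**Step 3: small-sample degrees of freedom.** The table uses normal quantiles. With 63/8, or about 8, groups in the CR arm, Satterthwaite-type degrees of freedom are about 23.5, 19.6 and 16.7 at ICC 0.01, 0.05 and 0.10. Power of the corresponding t-test is 75.3%, 69.2% and 62.4%. Attrition is not included in any of these figures.

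**Step 4: a secondary outcome.** For the Scale for the Assessment of Negative Symptoms (SANS) the protocol gives a detectable difference of 6.54 points and judges power sufficient because treatments have reduced the score by more than 7. At m = 8 and ICC = 0.05 the detectable difference becomes 6.54 × √(2.35/2) = 7.1, which uses up that margin.

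**The case against.** **The ICC is unknown and may be small for the primary outcome.** BACS is a performance test. Much of the training that bears on it is individual: computer work in session and at home, plus 12 one-to-one sessions. The group-psychotherapy part targets social cognition, which other, exploratory instruments measure. At ICC 0.01 the loss is about one percentage point of power. This stands. It makes the size uncertain but leaves the direction unchanged for any positive ICC.

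**Eight is a maximum and the groups are open.** Membership changes and overlaps, so discrete clusters of eight do not exist and the design effect is an approximation. This stands, and is why a range over m is shown.

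**The article condenses a fuller document.** A group or therapist term could be specified in a full protocol or SAP that is not shown. A reader might infer that such a term has been ruled out, but the article is only silent. The sample-size part does not depend on this, because its inputs are fully stated and return 63 without a design effect.

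**Stronger readings that the protocol does not support:**
- That the unadjusted test is biased in favour of CR. An understated standard error does not shift the estimate, and the excess false positives fall in both tails. At m = 8 and ICC 0.05, 7.06%/2 = 3.5% falls on each side instead of 2.5%.
- That a small therapist team treats everyone. Only the staffing of a group is given, not the total number of therapists.
- That controls are strictly unclustered. Some may share clinicians or facilities. What can be said is that the trial creates no groups among them.

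**Conclusion.** The point holds in conditional form. The 80% power assumes that CR patients who share groups or therapists are uncorrelated, and the analysis as described gives no check of that assumption.

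Over an assumed ICC of 0.01 to 0.10 and groups of 4 to 8, power by the normal approximation runs from 79.5% down to 67.6%, and type I error of the unadjusted test from 5.2% up to 9.2%. The consequence is negligible at the low end, which is plausible for BACS, and material at ICC 0.05 and above with groups near the maximum. A reader might conclude that the standard error is certainly too small. The protocol does not establish that, because it gives no ICC.

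**What to change.** 1. State beside the sample size that 80% power assumes no correlation within CR groups, and give the range above. Say the same of the secondary-outcome power statements.
2. Record group, lead therapist and entry date for each CR patient. The Trial status section reports 19 of 126 patients randomised by November 2014, so at that point this could still be done prospectively for most.
3. Leave the primary analysis unchanged. Beside it, pre-specify a partially nested sensitivity model with a cluster term in the CR arm only (for example group by calendar period of entry, since groups are open) and small-sample degrees of freedom. Report both intervals.

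The cost is a few recorded fields and one further model. The sensitivity interval will be somewhat wider. With few clusters the variance component will be imprecise, and if one team treats every CR patient a therapist variance cannot be estimated. A reader might want the superiority claim to require that this second interval also excludes zero. That imprecision is a reason not to make it a formal gate; it should inform how firmly the result is stated.
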